**Figure 1 figure1:**
[figure not shown]
Flowchart of process a new participant goes through upon registration.

**Figure 2 figure2:**
[figure not shown]
Brain Aging Monitor homepage.

**Figure 3 figure3:**
[figure not shown]
Screenshot of feedback module on nutrition questionnaire.

### Use of Health Behavior Change Theory

A description of the behavior change techniques used is given using the taxonomy provided by Abraham and Michie [59]. This paper provides researchers with 26 behavior change techniques based on behavior change theories to be used while designing an intervention. As the BAM is a self-guided, voluntary online intervention, the majority of participants will be in the last three stages of the Transtheoretical Model (TTM): the preparation, action, and maintenance phases [60]. The BAM guides participants from preparation phase (informing) to action phase (goal setting, short-term self-monitoring) to maintenance phase (long-term self-monitoring). As participants enroll in the BAM, the three stages of the TTM are facilitated instantaneously. And for every behavior, the participant can choose the most appropriate phase to start with. When the preparation phase is chosen, the knowledge database for that behavior is the most suitable starting point. Providing a participant with information is in accordance with the Information-Motivation-Behavioral Skills Model (Fisher).

When participants decide to enter the action phase of the TTM and become active goal-setters, they get an appropriate list of instructions and tips. Setting active behavioral goals is a part of most renowned behavior change theories such as the Theory of Planned Behavior (TPB) [61] and the Social Cognitive Theory (SCT) [62]. In line with the SCT, general encouragement is provided when goals are set and (partially) accomplished. While working with the tips and tools, participants will monitor their behavior. Bandura notes in his SCT that self-directed change can be promoted with features that allow program participants to set realistic goals, provide them with instructions and tips to reach these goals, and to allow for detailed self-monitoring of their own behavior over time [63,64]. Using GAS prompts a participant to set specific lifestyle goals, the buddy system prompts the review of behavioral goals, the short-term monitoring system prompts self-monitoring of behavior, and evaluating their own performance gives the participant feedback on their own behavior. The instructions and tips, when of additional value, include a list of commonly heard behavioral barriers and reasons why these barriers are either invalid or on how to overcome them, which is part of the SCT. Another possible instruction was to set up a behavioral contract with a person close to the goal-setter to create a form of peer pressure or control, which is in line with the theory of operant conditioning [59]. Among the instructions and tips, when applicable, is the suggestion to form “if-then” implementation intentions [63]. These if-then implementation intentions partially ease the transformation of behavior but also aid in relapse prevention, as these actively trigger the goal-setter to identify risk situations and come up with an appropriate action if the occasion arises (eg, IF my friends keep asking me to drink beer, THEN I will firmly tell them that I am drinking water this evening). Finally, the goal that can be set to reduce stress and optimize satisfaction with life aims at stress reduction through various methods (eg, yoga, mindfulness).

After the completion of a goal, follow-up is built into the system by automatically re-evaluating changed behavior on a monthly basis. Also, using an automated email reminder system, the BAM aims to maximize adherence to the program, providing follow-up prompts. To summarize, in accordance with the taxonomy by Abraham and Michie, 13 out of 26 behavior change techniques are used in the BAM (#1, 4, 5, 6, 8, 10-13, 16, 18, 23, and 24) [59].

### Research Questions and Outcome Measures

Our primary research questions are the following: (1) Is successful health behavior change related to better cognitive aging patterns over time? Change scores will be calculated by subtracting baseline scores from scores at year 1 and year 2, (2) Does the BAM facilitate health behavior change? (see Multimedia Appendix 3 for the construction of the overall lifestyle score), and (3) Does the BAM facilitate health behavior change in certain specific lifestyle areas better than others?

Our secondary research questions are as follows: (1) Is there a dose-response relationship between the number of goals participants set and the expected amount of health behavior improvement? and (2) Does the BAM increase feelings of self-efficacy in health-related behavior and a change in self-control scores from baseline to 1 and 2 years of intervention, as measured with the Self-Control Scale [56]. In other words, does the BAM increase feelings of being in control of one’s life?

Our primary outcome measures are (1) cognitive change over time, (2) overall lifestyle change over time, and (3) specific lifestyle changes over time. The secondary outcome measures consist of (1) number of goals set, (2) change in self-efficacy, and (3) change in self-control.

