### Study Design

For this study, we will use a quasi-experimental longitudinal pre-posttest design, with measurements at baseline and after 12 and 24 months. Only Dutch individuals within the Netherlands will be recruited. The intervention website is programmed in Dutch and as such will not be feasible for implementation outside the Netherlands. Since the Brain Aging Monitor is an eHealth intervention and the Netherlands has an Internet penetration of 94% of all households [41], there is no limit to its potential reach within the Dutch-speaking community. There are no regional restrictions that keep uptake of the intervention pinned to the region of the research institute. Since the entire intervention is based on self-management, contact with the research team is strictly limited to technical support. Considering the fact that the protocol relates to a pragmatic field study that will recruit both at an individual and organizational level, we cannot give an accurate estimate of the number of sites needed to obtain the necessary number of participants. For a sample size calculation, we refer to the description of sample size (Nederlands Trial Register: NTR4144).

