### Participant Timeline

The timeline for the BAM is straightforward (see Figure 1). Participants need to register only once. Immediately after registering, email validation, and the informed consent form, the lifestyle questionnaires are available. Once the lifestyle questionnaires have been completed, the BAM-COG becomes available. Seven days after subscription, the personality questionnaires appear in the personal dashboard. These features are all presented again to the participant 365 and 730 days after their baseline completion. The GSM, STMS, and LTMS are continuous processes from the moment they first become available to the participant. After 1 year (365 days), the data will be collected for preliminary secondary outcome analysis. After the 2-year follow-up (730 days), the data will be used for analysis of both primary and secondary outcomes. The nature of the grant requires that the intervention remain online even after data collection is finished for the initial study period and that the BAM remain open to the public after the study is completed. Adaptations to the program can be made at this time, according to study outcomes.

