### Sample Size

We aim for a group size of 200 to find a 15% reduction on the risk factors (power calculation based on alpha <.05; power of 0.8; two-tailed; n=166; ±20% dropout).

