### Statistical Analyses

#### Intervention Effects

Primary analyses will be unadjusted. Depending on the distribution of continuous, categorical, and interval outcomes, an appropriate distribution and relevant statistical models will be used. These models will assess intervention effects at end-of-intervention (1-year and 2-year) as well as the difference between 1- and 2-year measurements. Baseline characteristics will be compared between groups using *t* tests for continuous variables and chi-square tests for categorical variables. Mann-Whitney tests will be used when baseline data are not normally distributed. If necessary, multivariate analysis, including multi-analysis of variance and multiple regression, will be performed to adjust potential confounders, including baseline demographic and behavioral characteristics. The covariates associated with outcomes or contributing to a significant part of variation of used multivariate models will be adjusted as potential confounders. The final model will include these covariates or remove those that do not affect estimates, if models show evidence of overfitting.

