#### Secondary Analyses

Total set goals and specific lifestyle area goals will be reported descriptively. The changes of lifestyle within the goal setting group will be reported in absolute difference at end of intervention. The dose-response association between goals and change of lifestyle will be analyzed by multivariable linear regression model, and potential confounders will be adjusted. The change in self-efficacy and self-control scores will be reported in absolute difference at the end of the intervention. The association between the use of BAM and increased feelings of self-efficacy or self-control will be analyzed by multivariate analysis.

Analysis will be performed per protocol. The dropout in this pragmatic field study is likely to be high but can be considered a separate outcome for the implementation and feasibility of these types of intervention. As such, it represents valuable data about the quasi-experimental study design.

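### Primary question 1 rests on baseline change scores with no stated way of combining the waves; a joint model with year-specific slopes would use the year-1 data at no cost

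*Protocol article*

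**What the plan says.** The design has three waves, "with measurements at baseline and after 12 and 24 months" (Study Design). The first primary question asks: "Is successful health behavior change related to better cognitive aging patterns over time". The sentence that follows it, under Research Questions and Outcome Measures, reads "Change scores will be calculated by subtracting baseline scores from scores at year 1 and year 2".

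Under Intervention Effects the choice of distribution and model is left open, but the targets are time points: "These models will assess intervention effects at end-of-intervention (1-year and 2-year) as well as the difference between 1- and 2-year measurements". Participant Timeline assigns the 1-year data cut to a preliminary look at secondary outcomes and places the main analysis later: "After the 2-year follow-up (730 days), the data will be used for analysis of both primary and secondary outcomes".

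Under Secondary Analyses the article says analysis is per protocol and "The dropout in this pragmatic field study is likely to be high". No section says whether the two change scores enter one model or two, or what is done with a participant who attends year 1 but not year 2.

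**The concern.** A year-2-minus-baseline score contains no year-1 value and does not exist for anyone without a year-2 measurement. If each change score is analysed by itself, the 2-year result ignores one of the three waves and everyone who left after year 1, a group that should not be small given the dropout expected.

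The Abstract calls the relation between lifestyle change and cognitive aging the main outcome. The sample size was set for something else: "We aim for a group size of 200 to find a 15% reduction on the risk factors". So nothing shows spare power for this association. Two overlapping analyses of one question, with no statement of which is decisive, would add to the difficulty.

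**Working it through.** **The plan's own figure.** The sample size rests on "power calculation based on alpha <.05; power of 0.8; two-tailed; n=166; ±20% dropout". 166 × 1.2 = 199.2, which gives the target of 200; 166 / 0.8 = 207.5 would give 208. Enrolling 200 and losing 20% leaves 160. The 166 itself cannot be reproduced, because no baseline rate or SD is given, and it concerns risk-factor reduction rather than this association. It serves here only as an anchor: assume the year-2 change-score test has 80% power at 166. The standardized effect is then (1.960 + 0.842)/√166 = 0.217.

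**Assumptions (none from the article).** D1 and D2 are the cognitive changes from baseline, X1 and X2 the lifestyle changes, and each D is related to the X of the same year. Independent errors of equal variance at each wave give residual variance 2s² for each D and covariance s², so their correlation is r = 0.5. The correlation of X1 with X2 is ρ. A held step (X1 = X2) and a linear change (X1 = X2/2) both have ρ = 1. Of 200 enrolled, either 160 attend both follow-ups, or 160 attend year 1 and 120 attend year 2 (80%/60% retained, so 40/200 = 20% have year-1 data only).

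**Year-2 change score alone.** Noncentrality is 0.217 × √n2. For n2 = 160 this is 2.75, power 78.5%. For n2 = 120 it is 2.38, power 66.4%.

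**Joint model, year-specific slopes.** After scaling, the information terms are I22 = n2/(1−r²), I12 = −n2·r·ρ/(1−r²) and I11 = n2/(1−r²) + (n1−n2). The variance of the year-2 slope relative to the change-score analysis is n2/(I22 − I12²/I11), and power is Φ(noncentrality/√ratio − 1.960). Example with n1 = 160, n2 = 120, ρ = 1: I22 = 160, I12 = −80, I11 = 200, ratio = 120/(160 − 32) = 0.938.

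| n1 / n2 | ρ | Variance ratio | Power, change score | Power, joint | Gain (points) |
|---|---|---|---|---|---|
| 160/160 | 1 | 1.000 | 78.5% | 78.5% | 0 |
| 160/160 | 0.8 | 0.893 | 78.5% | 82.9% | 4 |
| 160/160 | 0.5 | 0.800 | 78.5% | 86.8% | 8 |
| 160/120 | 1 | 0.938 | 66.4% | 69.2% | 3 |
| 160/120 | 0.8 | 0.860 | 66.4% | 72.9% | 6–7 |
| 160/120 | 0.5 | 0.789 | 66.4% | 76.5% | 10 |

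Simulation with robust standard errors agreed with these values to within about 2 points. Other simulated scenarios gained up to about 13 points. More strongly correlated change-score errors raise the gain: if errors accumulate as a random walk, r = 0.71, and with 160 complete cases and ρ = 0.5 the ratio is 0.5/(1 − 0.125) = 0.571, power 95.3%, a gain of 17.

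**Joint model, one pooled slope, held step.** With 160 complete cases the pooled slope averages the two yearly slopes, and its variance is 1.5s² against 2s², ratio 0.75. With 160/120 the information is 120/1.5 + 40/2 = 100 against 120/2 = 60, ratio 0.60. If the year-1 slope is half the year-2 slope, the pooled slope is 0.75 of the year-2 slope with complete data, and (80 × 0.75 + 20 × 0.5)/100 = 0.70 of it with dropout. For a quarter the factors are 0.625 and 0.55.

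| Year-1 slope relative to year 2 | 160 complete: change score → pooled | 160/120: change score → pooled |
|---|---|---|
| equal | 78.5% → 88.8% | 66.4% → 86.8% |
| half | 78.5% → 66.4% | 66.4% → 57.6% |
| one quarter | 78.5% → 51.0% | 66.4% → 39.4% |

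Simulated values for the half-slope case with dropout ran from 57% to 61%.

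**The case against.** The strongest reply is that the key sentence defines variables and prescribes no test. The model is left open, both change scores can enter one repeated-measures model, and participants with only year-1 data do contribute to the year-1 score. The analysis plan, which is not at hand, may settle the matter. This stands in part: the article does not say that the waves are tested separately, and its silence on model detail is no fault in itself. What remains is that it ties the main question to these scores and to time-point effects, and that a 2-year score so built cannot use the year-1 data.

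A reader might also infer that the plan discards the middle wave and thereby gives up about 20 points of power. The article does not support this. It gives no SD, no lifestyle-cognition effect and no retention by wave. At 20% dropout a figure near 20 needs favourable assumptions, chiefly an equal slope in both years, and it is neither a bound nor a typical value.

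Finally, the 2-year association is a legitimate target, and a pooled slope is a different one. That objection holds fully against replacing the change scores by a common slope. If the association takes time to emerge, the pooled test loses about 9 to 27 points in the cases above. An interaction test may reveal the problem, but it does not restore the power.

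**Conclusion.** The point holds in limited form. Analysed as they stand, the 2-year change scores leave out the year-1 measurement and the participants who have only that follow-up; separate testing is the natural reading, not a stated fact.

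With the 2-year slope kept as the target, the loss is nil for complete data when lifestyle change is linear or a held step. It is roughly 3 to 13 points when about a fifth of those enrolled have year-1 data only or when lifestyle varies between waves. Stronger error correlation or heavier dropout can push it higher. Gains of about 10 to 20 points or more for a pooled slope rest on equal slopes in both years, which nothing in the article supports.

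The year-specific joint model did not lose power, beyond simulation noise, in any scenario tried. Two conditions apply. The gain from lifestyle variation assumes that cognition at each follow-up relates to lifestyle at that same follow-up. Using year-1-only participants assumes that the reason for missing year 2 is captured by the data observed. This is an efficiency and clarity improvement; the change scores are not invalid.

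**What to change.** State that baseline, year 1 and year 2 are analysed jointly in one longitudinal model with unstructured covariance, or with robust standard errors, and that every participant with at least one follow-up is included. Reconcile this with the per-protocol statement, so that a missing year-2 visit alone does not exclude anyone.

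- Primary question 1: keep year-specific lifestyle slopes through a slope-by-year interaction, name the 2-year association as the primary test, and report a common slope only as a supplementary estimate.
- Primary outcomes 2 and 3: take the 1-year, 2-year and 2-versus-1-year contrasts, which the article already lists, from one repeated-measures model.

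The cost is a few sentences of analysis wording. No visit, measurement or participant is added.

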### Participant Timeline

The timeline for the BAM is straightforward (see Figure 1). Participants need to register only once. Immediately after registering, email validation, and the informed consent form, the lifestyle questionnaires are available. Once the lifestyle questionnaires have been completed, the BAM-COG becomes available. Seven days after subscription, the personality questionnaires appear in the personal dashboard. These features are all presented again to the participant 365 and 730 days after their baseline completion. The GSM, STMS, and LTMS are continuous processes from the moment they first become available to the participant. After 1 year (365 days), the data will be collected for preliminary secondary outcome analysis. After the 2-year follow-up (730 days), the data will be used for analysis of both primary and secondary outcomes. The nature of the grant requires that the intervention remain online even after data collection is finished for the initial study period and that the BAM remain open to the public after the study is completed. Adaptations to the program can be made at this time, according to study outcomes.

### Sample Size

We aim for a group size of 200 to find a 15% reduction on the risk factors (power calculation based on alpha <.05; power of 0.8; two-tailed; n=166; ±20% dropout).

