**Methods:**

The Brain Aging Monitor study uses a quasi-experimental 2-year pre-posttest design. The Brain Aging Monitor is an online, self-motivated lifestyle intervention program. Recruitment is done both in medium to large organizations and in the Dutch general population over the age of 40. The main outcome measure is the relationship between lifestyle change and cognitive aging. The program uses different strategies and modalities such as Web content, email, online newsletters, and online games to aid its users in behavior change. To build self-regulatory skills, the Brain Aging Monitor offers its users goal-setting activities, skill-building activities, and self-monitoring.

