### Sequence Generation, Allocation Concealment Mechanism, Implementation, and Blinding

This pragmatic field trial does not use a control group. Therefore, sequence generation, allocation concealment, implementation, and blinding are not discussed.

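### The 80% power figure covers an unspecified lifestyle outcome, not the declared main outcome, and 200 enrolled with 20% dropout do not leave the 166 it assumes

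*Protocol article*

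**What the plan says.** The Sample Size section is one sentence. It sets the target and effect, "We aim for a group size of 200 to find a 15% reduction on the risk factors", and the remaining terms follow in brackets: "power calculation based on alpha <.05", then "power of 0.8; two-tailed; n=166", then dropout of about 20%. For the calculation itself, Study Design points elsewhere: "For a sample size calculation, we refer to the description of sample size (Nederlands Trial Register: NTR4144".

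The abstract declares the main outcome: "The main outcome measure is the relationship between lifestyle change and cognitive aging". Research Questions and Outcome Measures lists the same relationship as the first primary question, "Is successful health behavior change related to better cognitive aging patterns over time". It gives three primary outcome measures: cognitive change, overall lifestyle change and specific lifestyle changes.

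The design has one group, measured before and after: "This pragmatic field trial does not use a control group". Under Secondary Analyses, the article says that analysis is per protocol and that dropout will probably be high, without a figure.

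**The concern.** A reader will take the only power figure in the article as the power of the study. It belongs to a different endpoint from the one the abstract calls main. If the association between lifestyle change and cognitive change turns out null, the stated 80% invites the reading that a relevant association has been ruled out, although no power was given for that question.

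Two further points concern the figure itself. It speaks of the risk factors in the plural, while specific lifestyle changes are a primary outcome, so it can be read as promising 80% power in every area. And 166 is presented as what remains of 200 after about 20% dropout, which it is not.

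**Working it through.** **Inputs.** From Sample Size: two-sided alpha 0.05, power 0.80, n=166, enrolment 200, dropout about 20%. The article gives no baseline level, SD of change, within-person correlation or test. Throughout, z(0.975) + z(0.80) = 1.960 + 0.842 = 2.802.

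**1. Can n=166 be reproduced?** Not from the stated inputs alone. It can arise in a one-group pre-post design under added assumptions:
- McNemar test, net fall of 15 points, 48% discordant pairs (assumed): n = [(1.960·√0.48 + 0.842·√(0.48 − 0.15²)) / 0.15]² ≈ 165.1.
- Paired test of a mean, 15% fall from baseline: n=166 if the SD of change is 0.15·√166 / 2.802 ≈ 0.69 of the baseline mean (assumed).

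The figure is therefore possible but cannot be verified from the article.

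**2. What endpoint does it cover?** A reduction in risk factors fits overall or specific lifestyle change. It does not fit cognitive change or the association between the two. The article has no other size statement.

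**3. What does n=166 give for the main outcome?** I treat the association as a simple correlation (assumption) and use Fisher's z: power = Φ(atanh(r)·√(n−3) − 1.960), with √163 = 12.767.

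| r | atanh(r)·√163 | Power at n=166 |
|---|---|---|
| 0.10 | 1.281 | 25% |
| 0.15 | 1.930 | 49% |
| 0.20 | 2.588 | 74% |

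The correlation detectable with 80% power is tanh(2.802/√163) = 0.216.

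**4. Does 200 deliver 166?**
- 166 × 1.2 = 199.2, which rounds up to 200. This adds 20% of the evaluable number.
- 200 × (1 − 0.20) = 160. This is what 20% dropout leaves.
- 166 / (1 − 0.20) = 207.5, so 208 would be needed to retain 166.
- Going from 200 to 166 is a loss of 34/200 = 17%.

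**5. What does the shortfall cost?** With 166, a paired test has 80% power for a standardised change of 2.802/√166 = 0.217 SD. For that same effect with 160, power = Φ(2.802·√(160/166) − 1.960) = Φ(0.791) ≈ 78.5%. With 160 evaluable, the effects detectable with 80% power are:
- within-person change: 2.802/√160 = 0.221 SD
- correlation: tanh(2.802/√157) = 0.220

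**6. If dropout exceeds 20%.** The same formula for the 0.217 SD effect gives:

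| Dropout | Evaluable of 200 | Power |
|---|---|---|
| 20% | 160 | 78.5% |
| 30% | 140 | 73% |
| 40% | 120 | 66% |
| 50% | 100 | 58% |

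The rates above 20% are illustrative, since the article gives no figure for high dropout.

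**The case against.** The strongest reply is that the article condenses a calculation held in the registry, so a missing scale, baseline and test are not errors in themselves. Lifestyle change is also a listed primary outcome, so the calculation does address a primary outcome, and the sentence never claims power for cognition. All of this stands. It does not change which endpoint the sentence names or how its dropout arithmetic works out.

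A reader might go further and infer that 166 was computed for a trial with two independent groups, since 50% versus 35% gives (1.960 + 0.842)²·(0.25 + 0.2275)/0.15² ≈ 166.6 per group. The documents do not support this. No baseline rate appears in them, the match needs an assumed 50%, and step 1 shows that a one-group test can return about 166 as well.

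A reader might also infer very low power for less common risk factors. That requires each factor to be binary, the 15% to be relative, and an assumed prevalence. The article fixes none of these, and the effect may refer to the overall lifestyle score, for which prevalence plays no part. What can be said is only that the 80% is not shown to hold area by area.

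It can finally be objected that effects worked back from a fixed n say nothing about what is plausible or relevant. That is fair. They are offered as a statement of what the study can detect, not as target effects.

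**Conclusion.** The point holds in limited form, as something that should be corrected.

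- The stated 80% power concerns a lifestyle outcome and does not extend to the declared main outcome. If the association is analysed as a correlation, 166 evaluable give 80% power only from about r = 0.216, and 160 only from about r = 0.220.
- Neither the lifestyle outcome nor the scale of the 15% is identified, so 80% should not be claimed for each specific area.
- Enrolling 200 with 20% dropout leaves 160, not 166. The cost is about 1.5 percentage points of power (80% to 78.5%) for the effect that 166 would detect, and more if dropout is as high as the article anticipates.

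The correlation figures rest on Fisher's approximation for a simple correlation, and the power figures for within-person change on a normal approximation to a paired test. No error in the derivation of 166 itself has been shown.

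**What to change.** Keep the enrolment target of 200 and restate the Sample Size text as follows:

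1. State that 20% dropout leaves about 160 evaluable participants.
2. Tie the 15% reduction and the 80% power to one named lifestyle outcome, say whether the 15% is absolute or relative, and align this with the registry calculation. Give the power at 160.
3. Add that 160 evaluable give 80% power (two-sided 5%) only for a correlation of about 0.22 between lifestyle change and cognitive change, or for a within-person change of about 0.22 SD, and less power if dropout exceeds 20%.
4. Report the association and the area-specific outcomes with confidence intervals, and claim no 80% power for the specific areas.

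This costs a short rewording and no extra enrolment. The stated power becomes slightly less favourable.
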